### Ancillary studies

Building on the strengths and interests across the iBEAt participating centres, six ancillary studies have been incorporated within the central iBEAt study. Participants taking part in the ancillary studies will be recruited from the central iBEAt study at the relevant sites.

#### Ancillary study 1

To examine whether MRI and US based imaging biomarkers correlate with histopathological markers of DKD and discriminate different renal lesions in this T2D cohort. For this ancillary study, led by Bari University, iBEAt participants will undergo a renal tissue core biopsy. All biopsies will be digitalised and characterised by light microscopy (hematoxylin-eosin, periodic acid-Schiff, silver methenamine, and Masson’s trichrome), immunofluorescence microscopy (with the use of antisera against IgG, IgM, IgA, C3, C4, C1q and fibrinogen) and electron microscopy. Glomerular and vascular lesions, interstitial cell infiltrate, fibrosis and tubular atrophy will be quantified to classify patients accordingly [30]. Samples will also be processed and stored for later biomarker discovery. The procedures for processing, storing and capturing meta-data regarding the renal biopsy tissue are described in more detail in additional file 4.0.

#### Ancillary study 2

To examine whether MRI-based measurements of renal blood flow correlate with H_2_O^15^-positron emission tomography (PET), considered to be a reference measurement. For this ancillary study, led by Turku University, a direct comparison of MRI and PET-based measurements of renal blood flow will be performed in a cohort of iBEAt participants. Renal perfusion will be assessed during hyperaemia with both systems.

#### Ancillary study 3

To validate automated or semi-automated processing of multiparametric renal MRI. In its current form the generation of biomarkers from complex functional MRI scans involves significant manual intervention as well as automated but slow iterative optimisation methods. In this study, led by Sheffield University, a subset of the iBEAt data will be used as training data to develop an ideally automated approach for image processing, which will then be validated on the remaining test data against the manual results.

#### Ancillary study 4

To investigate the longitudinal changes in MRI and US based biomarkers, compare them against changes in eGFR and other known markers, and determine whether changes in imaging biomarkers precede DKD progression as assessed by eGFR decline. For this study, performed by the Universities of Bordeaux and Exeter, a cohort of 100 patients will receive repeat MRI and US after 2 years, and changes in imaging biomarkers over that period will be correlated against changes in eGFR and other assessments.

#### Ancillary study 5

To examine whether the glycocalyx, microvascular function and structure (retinal and skin) are (1) altered in microalbuminuria (2); associated with DKD progression as assessed by eGFR decline and (3) associated with novel MRI and US imaging DKD biomarkers. For this study, led by Exeter University, iBEAt participants will also undergo comprehensive microvascular assessments (including non-invasive estimation of sublingual endothelial glycocalyx integrity, retinal vascular oxygenation and skin maximum hyperaemia) at baseline and at 2 years follow-up.

#### Ancillary study 6

A pilot study to examine whether the findings in T2D can be extrapolated to Type 1 diabetes. In this ancillary study, led by Bordeaux University, a cohort of 50 patients with Type 1 diabetes for 15 years or more will be assessed using the same procedures as the Type 2 cohort and observed findings / trends will be compared across the two populations.

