**Methods:**

iBEAt is a prospective multi-centre observational cohort study recruiting 500 patients with type 2 diabetes (T2D) and eGFR ≥30 ml/min/1.73m^2^. At baseline, blood and urine will be collected, clinical examinations will be performed, and medical history will be obtained. These assessments will be repeated annually for 3 years. At baseline each participant will also undergo quantitative renal MRI and US with central processing of MRI images. Biological samples will be stored in a central laboratory for biomarker and validation studies, and data in a central data depository. Data analysis will explore the potential associations between imaging biomarkers and renal function, and whether the imaging biomarkers improve the prediction of DKD progression. Ancillary substudies will: (1) validate imaging biomarkers against renal histopathology; (2) validate MRI based renal blood flow measurements against H_2_O^15^ positron-emission tomography (PET); (3) validate methods for (semi-)automated processing of renal MRI; (4) examine longitudinal changes in imaging biomarkers; (5) examine whether glycocalyx and microvascular measures are associated with imaging biomarkers and eGFR decline; (6) explore whether the findings in T2D can be extrapolated to type 1 diabetes.

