### Statistical considerations

#### Sample size

There are insufficient a priori data available to perform a reliable formal power calculation for this study. Thus, a more pragmatic approach was adopted, with the sample size taking into account the feasibility aspects of the study, for example, the number of imaging facilities and the estimated rate of recruitment in each centre. This produced a target population of 500 patients, which will result in the largest quantitative imaging DKD study, to date, both in terms of patient numbers and regarding patient follow-up. Participants will be recruited across various stages of DKD, as measured by ACR (A1, A2, A3) and eGFR (G1 + G2, G3). This will produce a heterogeneous population enabling the evaluation of the associations between imaging biomarkers and DKD in T2D patients.

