#### Statistical analysis plan

Descriptive statistics of all covariates across the study centres will assess the bivariate relationships between sets of related covariates. A cross-sectional analysis will be performed using data collected at baseline, as well as a longitudinal analysis using the imaging data collected at baseline and blood and urine markers collected annually. Given the large number of covariates in the study, a variable selection and regularisation method such as LASSO [28] or the elastic net regularisation [29] will be used. Modelling will use linear models for the cross-sectional analyses, and linear mixed effects models for the longitudinal analysis. The analyses will be performed separately in each ACR / eGFR stratum, and the modelling of the whole cohort will account, whenever possible, for differences in potential associations across the strata. We will adjust for multiple comparisons as needed. If any renal imaging biomarkers are identified as promising early markers of DKD progression, they will be used in risk prediction. Their predictive accuracy as measured by prediction error, receiver operating characteristics curve (ROC) and the area under the ROC (area under the curve, AUC) will be evaluated using cross-validation. A conservative approach will be adopted in all analyses, for example, limiting the number of models fitted and statistical tests performed. All analyses will be treated as exploratory and hypotheses generating, rather than hypothesis testing.

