iBEAt setup started in September of 2016 and is the first study to respond to the clinical need for systematically collected evidence at a larger scale and across institutions, with well-validated methods linking up the imaging findings with other sources of data so the added value can be identified. In that sense, iBEAt is inspired by the landmark study CRISP (Consortium for Radiologic Imaging Studies of Polycystic Kidney Disease) [36] - the first multi-centre cohort study exploring a quantitative MRI biomarker (TKV) in CKD and a foundation for the aforementioned FDA qualification of TKV. Like CRISP, iBEAt has built in a technical validation phase of the imaging biomarkers by including a repeatability study on all scanner types deployed in iBEAt, and by calibrating between-scanner differences through a travelling test object developed by the National Institute of Standards and Technology [37]. Also following the example of CRISP, iBEAt is committed to sharing the technical details of its imaging protocols and expertise in image processing and quality assurance – not only to facilitate the cost and setup of future studies but also to maximise alignment and future opportunities for pooling the data.

The integration of the ancillary studies into iBEAt will provide valuable information on the pathogenesis of DKD and the clinical utility of these imaging biomarkers. Crucially, they will explore the association of renal based imaging biomarkers against histopathological markers and different histological lesions of DKD, validating the imaging biomarkers and substantiating their clinical utility. MRI-based renal perfusion measurements will also be validated against PET renal perfusion measurements. The potential automation of the MRI image processing will streamline a labour-intensive process, thereby increasing the clinical applicability of the assessments. The microvascular assessments, including the examination of glycocalyx integrity and endothelial function, will provide invaluable information on the pathogenesis and heterogeneity of DKD, and may well aid the identification of individuals with fast progressing DKD. For example, we hypothesise that individuals with T2D and early signs of perturbations to the glycocalyx will be at an increased risk of DKD progression.

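### Ancillary study 2 is described as validating MRI renal blood flow against PET, but its stated aim is correlation, which cannot show agreement

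*Protocol article*

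**What the plan says.** Three places in the protocol article bear on this.

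- **Ancillary studies, Ancillary study 2.** The aim is "To examine whether MRI-based measurements of renal blood flow correlate with" water PET, which is "considered to be a reference measurement". The design sentence adds that "a direct comparison of MRI and PET-based measurements of renal blood flow will be performed in a cohort of iBEAt participants". The last sentence reads "Renal perfusion will be assessed during hyperaemia with both systems".
- **Abstract, Methods.** The same substudy is listed as one that will "validate MRI based renal blood flow measurements against" PET.
- **Discussion.** "MRI-based renal perfusion measurements will also be validated against PET renal perfusion measurements".

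The article names no measure of bias, no limits of agreement, no concordance or intraclass coefficient and no acceptable difference for this comparison. It also states no correlation threshold. Its general position, under Statistical analysis plan, is that "All analyses will be treated as exploratory and hypotheses generating, rather than hypothesis testing".

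**The concern.** MRI and PET are meant to measure the same quantity in the same people, and one of them is designated the reference. The question that bears on validation is how far an MRI value lies from the PET value, on average and for an individual patient. A correlation coefficient answers a different question: whether patients with higher PET flow also tend to have higher MRI flow. It does not change if every MRI value is shifted or multiplied by a positive constant, and it rises with the spread of the patients even when measurement error is unchanged.

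The mismatch is therefore between the aim as worded and the claim made for it. If the aim were carried out literally, a high r could be reported as validation while the size of any bias in absolute flow remained unknown. The Methods list cortical perfusion and renal artery blood flow among the quantitative MRI biomarkers, so the absolute scale is of interest. The repeatability scans address within-site variability and the phantom addresses between-site calibration. Neither is described as testing the accuracy of blood flow in patients.

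**Working it through.** **No figure to reproduce.** The article gives no sample size, threshold or margin for this substudy. For the study as a whole it says "There are insufficient a priori data available to perform a reliable formal power calculation for this study". These gaps are not counted as faults here; they mean that any size has to be illustrated.

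**Step 1: algebra, no assumption needed.** For MRI value M, PET value P, any constant c and any d > 0, corr(c + dM, P) = corr(M, P). Offset and scale errors leave r untouched.

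**Step 2: illustration.** These assumptions are not from the article. PET has mean 100 (arbitrary units) and SD s = 15, 25 or 35, that is, a CV of 15%, 25% or 35%. MRI = b × PET + error, with error SD = b·s·√(1/0.90² − 1), so that r = 0.90 throughout.

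- Bias = 100(b − 1)
- Var(MRI) = (b·s/0.90)²; covariance = b·s²
- Lin's concordance CCC = 2·cov / [s² + Var(MRI) + bias²]
- 95% limits of agreement = bias ± 1.96·√[(b − 1)²s² + error SD²]

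Worked case, MRI 40% low (b = 0.6), CV 25%:

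- error SD = 0.6 × 25 × 0.484 = 7.27
- Var(MRI) = (15/0.90)² = 277.8; cov = 0.6 × 625 = 375; bias = −40
- CCC = 750 / (625 + 277.8 + 1600) = 0.30
- SD of differences = √(10² + 7.27²) = 12.36
- limits = −40 ± 24.2, that is −64.2 to −15.8

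| MRI relative to PET | r | CCC at CV 15% / 25% / 35% | Bias | Limits at CV 25% |
|---|---|---|---|---|
| unbiased | 0.90 | 0.895 / 0.895 / 0.895 | 0 | −23.7 to 23.7 |
| 20% low | 0.90 | 0.45 / 0.66 / 0.76 | −20 | −41.4 to 1.4 |
| 40% low | 0.90 | 0.14 / 0.30 / 0.44 | −40 | −64.2 to −15.8 |
| 50% high | 0.90 | 0.20 / 0.39 / 0.52 | +50 | 6.8 to 93.2 |

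The r column cannot separate the first row from the others. The agreement columns can.

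**Step 3: dependence on spread.** Take an unbiased MRI with fixed error SD 15. The limits of agreement are ±1.96 × 15 = ±29.4 whatever the patients. But r = s/√(s² + 15²), which is 0.56, 0.80 and 0.89 for PET SD 10, 20 and 30. The same instrument gets three different correlations.

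**Step 4: how little a significant correlation shows.** Using Fisher's z, n = [(1.960 + 0.842)/atanh(r)]² + 3, rounded up, for two-sided 5% and 80% power. This gives 30 patients for a true r of 0.5, 14 for 0.7 and 7 for 0.9. The article does not say that significance is the criterion; the figures only show that a non-zero correlation would be a weak result.

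**The case against.** The best defence is that this is three sentences in a condensed article. Correlation appears as the verb of an aim, not as an endpoint with a threshold, and the article uses the same verb loosely in ancillary studies 1 and 4. The sentence announcing a direct comparison is neutral about method and could cover an agreement analysis set out in an ancillary protocol that is not shown. The choice of agreement statistic is detail that an article may leave out.

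Part of this stands. The absence of a named statistic is not a fault in itself. What remains is that the article does state an aim, that aim is correlation, and elsewhere it calls the result validation. The direct-comparison wording allows agreement to be assessed but does not commit to it.

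Four stronger readings are tempting, and the article does not support them.

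- *A badly biased MRI method would be passed as valid.* No acceptance rule is stated, so nothing in the text passes or fails a method.
- *A scaling error would slip unnoticed into the pooled multi-vendor analysis.* The substudy is led by one centre. If only that site's scanner is compared with PET, even a full agreement analysis could not reveal differences between vendors; those are addressed separately by the repeatability scans and the phantom, although the article does not show that the phantom tests flow. The main analyses are linear and mixed models of association, in which a scaling error common to all sites rescales a coefficient without changing the strength of the linear association.
- *Validation is planned in hyperaemia only.* The article says perfusion is assessed during hyperaemia with both systems. It does not say that this is the only state, and it is silent on resting PET.
- *The cohort's heterogeneity will inflate r here.* Heterogeneity is described for the 500-patient study, not for the PET subset.

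**Conclusion.** The concern holds as a mismatch between aim and claim: a study whose stated aim is correlation cannot, on that aim, support the statement that MRI is validated against PET. That r ignores bias is algebra and rests on no assumption. The size is illustrative. With r held at 0.90, concordance falls from 0.895 to between 0.76 and 0.14 as the MRI under-reading goes from 20% to 40% and the CV from 35% down to 15%. The means, CVs and biases are assumed and are not estimates for this study.

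Severity is modest. The study is ancillary, all analyses are declared exploratory, and neither the primary nor the secondary objective depends directly on it. The consequence is confined to what can be said about absolute MRI flow values.

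**What to change.** Restate the aim of ancillary study 2 as assessing the agreement of MRI with PET renal blood flow, and report:

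- mean bias and 95% limits of agreement, each with a confidence interval, on the log scale if differences grow with flow;
- a check for proportional bias;
- a concordance coefficient;
- Pearson r as a descriptive supplement only.

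It would help to state in advance what difference would be acceptable. Word the validation statement in the abstract and Discussion so that it applies to the scanner or scanners and the flow state actually compared: hyperaemia, and rest only if paired resting values exist.

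The same paired measurements suffice, so the cost is a little more analysis and possibly a less favourable validation statement. The fix does not require resting scans to be added. If none are acquired, the statement is simply limited to hyperaemia.

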### Patient and public involvement

Patient and public involvement and engagement is a significant component of the iBEAt study. Potential participants have played an important role in iBEAt, reviewing the protocol to ensure the feasibility of the study design (core and ancillary studies) as well as contributing to the development of patient facing documents (e.g. patient information sheets), ensuring that they are clear and informative. Participants within the iBEAt study will play an integral role in the dissemination of the study results to the wider, non-expert population. Within the BEAt-DKD consortium discussions with patient representatives, ranging from experienced patient advocates to iBEAt participants, will help inform how research from the BEAt-DKD consortium is taken forward to implement a more precision medicine based approach in DKD into clinical practice; for example, validation and qualification of new biomarkers by regulatory agencies, optimising clinical study design and integration in the regulatory process of drug registration. Indeed, this has already commenced with an iBEAt participant and other patient representatives attending the 2nd BEAt-DKD Stakeholders’ symposiums in April 2019 [31].

## Discussion

Quantitative and functional imaging of the kidney has been an active topic of research in the MRI physics and radiology community for over two decades [32], but the last few years have seen an explosive growth in clinical interest. The first international meeting on functional renal MRI was held in 2015 and attendance has been increasing steadily in subsequent meetings [33–35]. In 2017, a pan-European network of researchers in renal MRI (www.renalmri.org) was funded for 4 years by the European Cooperation in Science and Technology (www.cost.eu). In 2018, Nephrology Dialysis Transplantation published a special issue on renal MRI with a clinical position statement supported by over 30 authors including leading European nephrologists [9]. In the same year, in the US, the National Institute of Diabetes and Digestive and Kidney Diseases (NIDDK) at the National Institutes of Health (NIH) conducted a workshop on renal imaging to review the state-of-the-art and plan potential future endeavours [7]. Also in 2018, the UK Renal Imaging network (UKRIN) received a 3-year partnership grant to create a national infrastructure for quantitative renal MRI. In 2020, UKRIN has received funding for a 10 year cohort study in 500 CKD patients starting 1 sept 2020 (AFiRM study; principal investigator: [name], University of Nottingham).

iBEAt setup started in September of 2016 and is the first study to respond to the clinical need for systematically collected evidence at a larger scale and across institutions, with well-validated methods linking up the imaging findings with other sources of data so the added value can be identified. In that sense, iBEAt is inspired by the landmark study CRISP (Consortium for Radiologic Imaging Studies of Polycystic Kidney Disease) [36] - the first multi-centre cohort study exploring a quantitative MRI biomarker (TKV) in CKD and a foundation for the aforementioned FDA qualification of TKV. Like CRISP, iBEAt has built in a technical validation phase of the imaging biomarkers by including a repeatability study on all scanner types deployed in iBEAt, and by calibrating between-scanner differences through a travelling test object developed by the National Institute of Standards and Technology [37]. Also following the example of CRISP, iBEAt is committed to sharing the technical details of its imaging protocols and expertise in image processing and quality assurance – not only to facilitate the cost and setup of future studies but also to maximise alignment and future opportunities for pooling the data.

The integration of the ancillary studies into iBEAt will provide valuable information on the pathogenesis of DKD and the clinical utility of these imaging biomarkers. Crucially, they will explore the association of renal based imaging biomarkers against histopathological markers and different histological lesions of DKD, validating the imaging biomarkers and substantiating their clinical utility. MRI-based renal perfusion measurements will also be validated against PET renal perfusion measurements. The potential automation of the MRI image processing will streamline a labour-intensive process, thereby increasing the clinical applicability of the assessments. The microvascular assessments, including the examination of glycocalyx integrity and endothelial function, will provide invaluable information on the pathogenesis and heterogeneity of DKD, and may well aid the identification of individuals with fast progressing DKD. For example, we hypothesise that individuals with T2D and early signs of perturbations to the glycocalyx will be at an increased risk of DKD progression.

iBEAt has greatly benefitted in its setup from study documents and standard operating procedures (SOPs) provided by other investigators, in particular the PROVALID [27] and NEPTUNE [26] studies. In turn, iBEAt is committed to a “pay-it-forward” philosophy and will aim to share its study documentation and procedures widely for use by other investigators. iBEAt collaborators are also committed to maximise the opportunities for data sharing in order to increase the lifetime value of their research data as assets for human health and to do so timely, responsibly, with as few restrictions as possible, in a way consistent with the law, regulation and recognised good practice. Beyond data, iBEAt will aim to form a powerful resource for future biomarker discovery sources by collecting a rich collection of blood and urine samples in its central biobank. These will be made available for external investigators subject to formal application and approval by the iBEAt Steering Committee.

After a 2-year setup period the first study participant was recruited into iBEAt in October 2018. First results on technical validation of MRI methods on the reference scanner are expected at the end of 2020. The projected deadline for recruitment was 1 September 2020 and first results on the primary objective (cross-sectional analysis of baseline data) were expected to be made public in 2021. Completion of follow-up data was expected in September 2023, with results on the longitudinal analysis expected to be submitted for publication in 2024. These timelines will be affected by a pause in recruitment during the COVID-19 pandemic, but at submission of this manuscript (April 2020) the exact implications are not yet clear.

